**Methods:**

The clinical study (DRKS00026624) includes two randomized controlled intervention trials with parallel groups, for patients with elective cardiac catheterization and practitioners at the catheterization lab, in two clinic sites of the Ernst-von-Bergmann clinic network in Brandenburg, Germany. Both groups received different interventions for stress management. The intervention for patients comprises a psychoeducational video with different stress management technics and additional a standardized medical information about the cardiac catheterization examination. The control condition includes the in hospitals practiced medical patient education before the examination (usual care). Primary and secondary outcomes are measured by physiological parameters and validated questionnaires, the day before (M1) and after (M2) the cardiac catheterization and at a postal follow-up 6 months later (M3). It is expected that people with standardized information and psychoeducation show reduced complications during cardiac catheterization procedures, better pre- and post-operative wellbeing, regeneration, mood and lower stress levels over time. The intervention for practitioners includes a Mindfulness-based stress reduction program (MBSR) over 8 weeks supervised by an experienced MBSR practitioner directly at the clinic site and an operative guideline. It is expected that practitioners with intervention show improved perceived and chronic stress, occupational health, physical and mental function, higher effort-reward balance, regeneration and quality of life. Primary and secondary outcomes are measured by physiological parameters (heart rate variability, saliva cortisol) and validated questionnaires and will be assessed before (M1) and after (M2) the MBSR intervention and at a postal follow-up 6 months later (M3). Physiological biomarkers in practitioners will be assessed before (M1) and after intervention (M2) on two work days and a two days off. Intervention effects in both groups (practitioners and patients) will be evaluated separately using multivariate variance analysis.

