### Sample Size Determination

We calculated the sample size for two patient groups for two measurement points based on a pilot study. The sample was powered to assume a medium effect size (*d* = 0.25) and a minimum detectable clinical difference of 0.5 standard deviation on the (z-standardized) main criterion: perceived stress. For the main criterion, the power for significant group differences is 1-β = 0.93 with a case number of *N* = 60 people per group (38). As the sample for the practitioners was limited to all members of the catheterization lab of the clinic who fulfill the inclusion criteria, a sample size determination was not required.

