### Statistical Analysis

All statistical analyses will be performed using SPSS. The data of the practitioners will be mainly analyzed descriptively due to the small sample size. Interferential statistics will be used to identify group differences. A comparison with norms of the German general population will be performed to assess the stress of the practitioners in the cardiac catheter laboratory. Baseline and post-interventional physiological data like circadian profile slopes of HRV and derived indicators (SDNN, RMSSD, number and percentage of R-R intervals lower or >50 msec) as well as saliva cortisol, alpha-amylase and lysozyme measurements will be compared on an intraindividual level. The data of the patients will be analyzed according to a multivariate variance analysis (between-subject factor: intervention group vs. control group). Sociodemographic data, sedative medication, adherence to the intervention will be implemented as control variables or stratification variables for subgroup analysis. Statistical significance is set at *p* < 0.05 (two-sided) and effect sizes will be reported.

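### The patient trial is sized on perceived stress alone, but the only patient analysis named is a multivariate variance analysis, which read literally tests a different null and is not the test to which the stated power applies

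*Protocol article*

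**What the plan says.** Sample Size Determination bases the patient sample on one variable. It describes a calculation "for two patient groups for two measurement points based on a pilot study" and gives "a minimum detectable clinical difference of 0.5 standard deviation on the (z-standardized) main criterion: perceived stress". It states that "the power for significant group differences is 1-β = 0.93 with a case number of *N* = 60 people per group".

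Statistical Analysis names one analysis for the patients: "The data of the patients will be analyzed according to a multivariate variance analysis (between-subject factor: intervention group vs. control group"). The level is given as "Statistical significance is set at *p* < 0.05 (two-sided"). The Methods part of the Abstract agrees: "Intervention effects in both groups (practitioners and patients) will be evaluated separately using multivariate variance analysis".

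The Outcomes section lists several patient primary outcomes side by side: complications, sedative use, tension or strain by physiological parameters, perceived stress (PSS) and mood (POMS). Table 1 places the PSS-10 at M1 and M3 only.

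The article names no test of perceived stress on its own, and does not say how a multivariate result would lead to a conclusion about it.

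**The concern.** The sample size section asks whether the arms differ on perceived stress. A one-way multivariate variance analysis asks whether they differ on any linear combination of the outcomes entered. It can reject when perceived stress is unchanged, or when one outcome improves and another worsens. It can also fail to reject when perceived stress does differ, because that signal is tested with more numerator degrees of freedom.

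Two things are at stake. The first is interpretation: a significant result could be reported as the video lowering perceived stress when the test does not show that. The second is the power statement: 0.93 was worked out for one criterion, so it says nothing about the chance of success of the analysis that is named.

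**Working it through.** **Inputs from the article.** 60 per group, 1:1 allocation, two-sided 0.05, difference 0.5 SD on z-standardized perceived stress, stated power 0.93.

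**Assumptions, because the article does not give them.** The number of outcomes p in the multivariate model, and a common correlation r between them.

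**1. The plan's own figure.** For a direct two-group test the noncentrality is λ = (n/2)d² = 30d², with 1 and 118 df.
- d = 0.5: λ = 7.5, power 0.775.
- d = 0.25, the value in "powered to assume a medium effect size (*d* = 0.25"): λ = 1.875, power 0.27.

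Neither gives 0.93. An unstated correlation between the two measurement points can recover it:
- Repeated-measures variance analysis, between-group factor, effect size f = 0.25 (equal to d = 0.5 for two groups): λ = 0.0625 × 240/(1 + ρ). At ρ = 0.25, λ = 12.0 and power is 0.930.
- Baseline-adjusted model with d = 0.5: λ = 7.5/(1 − ρ²). At ρ = 0.6, λ = 11.72 and power is 0.92.

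So 0.93 is not shown to be wrong, but each of these routes is a test of a single criterion.

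**2. The multivariate test, only perceived stress shifted by 0.5 SD.** For two groups this is Hotelling's T², with p and 119 − p df, λ = 30D², and

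D² = 0.25 × [1 + (p − 2)r] / {(1 − r)[1 + (p − 1)r]}.

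For p = 5 (5 and 114 df):

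| r | D² | λ | Power |
|---|---|---|---|
| 0 | 0.250 | 7.50 | 0.51 |
| 0.3 | 0.308 | 9.25 | 0.61 |
| 0.5 | 0.417 | 12.50 | 0.77 |
| 0.7 | 0.680 | 20.39 | 0.95 |

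The direct unadjusted test has 0.775 throughout. For p = 2 the multivariate power is 0.68, 0.72, 0.80 and 0.93; for p = 7 it is 0.44, 0.56, 0.72 and 0.93.

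**3. All five outcomes shifted by 0.5 SD.** D² = 5 × 0.25/(1 + 4r). Power is 0.999 at r = 0, 0.90 at 0.3, 0.77 at 0.5 and 0.65 at 0.7.

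**4. A conclusion on perceived stress itself.** Suppose one is drawn only when both the multivariate test and the perceived-stress test are significant. In simulation (20,000 runs per case, p = 5, only perceived stress shifted) the probability is 0.49, 0.57, 0.67 and 0.76 at r = 0, 0.3, 0.5 and 0.7.

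**5. Perceived stress unchanged, one other outcome shifted by 0.5 SD.** By symmetry the rejection rates are those in the table, 0.51 to 0.95 for p = 5. These rejections are correct for the joint null, but they carry no information that perceived stress differs.

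**The case against.** The strongest reply is that *multivariate* was used loosely. Sizing for two groups and two measurement points suggests a repeated-measures analysis of perceived stress, and that analysis gives exactly 0.930 at ρ = 0.25. On that reading the mismatch disappears. It also disappears if perceived stress is tested on its own alongside the joint test, without gating. Neither can be ruled out, but the article says neither, and its list of several primary outcomes fits the literal reading. If the loose meaning was intended, the same one-sentence correction settles it.

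A second reply is that the outcomes entered and any follow-up tests belong in a fuller document. That is fair for the detail. The article does, however, name a test, and that test does not match the hypothesis it was sized for.

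Third, the number of outcomes is uncertain, and this stands. Sedative medication also appears as a control or stratification variable. In Table 1 the post-baseline PSS-10 is at M3, while mood and the physiological parameters are last measured at M2. A joint vector of PSS-10 with those outcomes at one post-baseline visit therefore cannot be formed. The choice of 5 is illustrative.

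Two stronger readings are tempting and are not supported:
- **The multivariate test always loses power.** It does not: with only perceived stress shifted it reaches 0.95 at r = 0.7, and with all five outcomes shifted it has 0.90 or more at r = 0 to 0.3. The article also expects effects on several outcomes.
- **Rejection when perceived stress is unchanged is type I error inflation.** In that scenario another outcome differs, so the joint null is false and the nominal 5% does not apply.

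**Conclusion.** The point holds in a limited form. The article sizes the patient trial for a difference on perceived stress and names only an analysis which, read literally, tests a joint and directionless null. A result from that analysis, significant or not, does not by itself answer the question the trial was sized for, and the 0.93 does not describe it. This follows from the definition of the test and needs no assumption about p or r.

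The size of the effect on power does need such assumptions. With 60 per arm, 5 outcomes and a 0.5 SD shift in perceived stress alone, it runs from 0.51 (r = 0) to 0.95 (r = 0.7), against 0.775 for the direct unadjusted test. It can therefore be a loss of about 26 points (0.775 − 0.51) or a gain in rejection rate that still is not a finding on perceived stress. The correction is worth making because it is specific and nearly free.

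**What to change.** In Statistical Analysis, name the test of the main criterion: a univariate linear model of PSS-10 at M3 (the only post-baseline PSS-10 in Table 1) by arm, with baseline PSS-10 as covariate, two-sided 0.05, reporting the adjusted difference and its 95% confidence interval. Keep the multivariate analysis, if wanted, as a supportive global test from which no claim on perceived stress is drawn. Align the Abstract.

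In Sample Size Determination, restate the power for that model with its assumed correlation between baseline and M3. Do not carry 0.93 over without it. For 0.5 SD and 60 per arm, λ = 7.5/(1 − ρ²) gives:
- ρ = 0: λ = 7.50, power 0.78
- ρ = 0.5: λ = 10.00, power 0.88
- ρ = 0.6: λ = 11.72, power 0.92

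The pilot study of 50 participants may inform ρ if it measured PSS twice; the article does not say.

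The cost is a few sentences and no new data, since PSS-10 is already collected at M1 and M3. The small downsides are that the multivariate test becomes supportive and that the restated power may fall below 0.93.

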### Experimental Procedure/Intervention

As both patients with an elective cardiac catheterization (CC) examination and practitioners at the catheterization lab face different stressors, both groups received different interventions for stress management.

The CC for the included study participants is elective (non-acute) and medically recommended to evaluate or confirm coronary artery disease, congenital heart disease, heart failure, heart valve disease or aorta dysfunction, heart muscle function and to decide for further treatment. On the admission day (M1), all patients get the usual medical patient information from a cardiologist and anesthetist and get prepared for the examination (fasting, no smoking, evaluation of medication). All patients that fulfill the inclusion criteria concerning age and CC examination will be randomly dedicated to intervention group and control group and subsequently contacted by a research assistant who present the study and its aims and answer all questions. All participants have to sign informed consent after receiving written and verbal information. Afterwards all participants receive the questionnaires for M1 (pre-intervention questionnaire) and only patients in the intervention group get and only patients in the interventions group get the intervention (see The intervention for patients). The next day (M2), all patients get the CC examination at the catheterization lab. During the CC the patient is usually awake and conscious as the hostipal policy is not to administer any tranquilizer, sedatives and anxiolytics as a routine before or during CC procedure. However, patients get sedatives if needed and the type of sedative and dose is documented in a questionnaire by physicians or nurses of the CC lab. After disinfection and local anesthetization of the insertion site (groin, wrist or rarely crook of the arm), the catheter is inserted through a plastic introducer sheath. The catheter is guided through the blood vessel to the coronary arteries and coronary angiography is done by injecting a contrast dye that is visible in X-ray images. The following further diagnostic and interventional procedures can be performed during a cardiac catheterization: myocardial biopsy, levocardiography, right ventriculogram, coronary angiogram, and treatments for narrowing or blockages in the blood vessels like balloon dilatation and stent placement. The aftertreatment includes a bed rest for several hours in the ward until the following day of discharge. The participants fill in the post-intervention questionnaire during the bed rest/stay in the ward (M2).

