
*The intervention for patients* focusses on a video-based standardized patient information about the cardiac catheterization examination and further involves a short patient education with different stress management technics. The video-based standardized patient information gives information about the aim and general process of the CC, like location and aftercare of the puncture, position of the participants during the examination how the procedure is monitored. Further information comprises potential but rare complications and side effects like additional interventions, circulatory disruptions, cardiac arrhythmia, bleedings and (temporary) pain. The second part of the video broaches the issue of stress management technics to handle anxiety, tension and malaise. It provides brief instructions for relaxation, meditation and guided imagery techniques as well as cognitive distraction tasks, and cognitive reframing. All cognitive techniques are easy to apply after one presentation and involve methods to stop negative thoughts, distract from unhelpful thought patterns, to guide attention and positive expectations, to lower tension and support relaxation. For example, the patient should recite the alphabet and imagine a positive thing or event for every letter that he/her would be able to do after the CC. The patient should guide his/her attention to their most pleasant vacation and reactivate the feelings and thoughts present at that time. If a patient feels discomfort or pain, he/she should guide his attention to his/her big toe or left hand for cognitive distraction. The video encourages the patient to speak to the doctors and nurses about complaints and needed assistance. The video is shown to the patients the day before the CC via a tablet bedside in the clinic and is complementary to the non-standardized patient education by the medical doctor that is clinical routine for both intervention and control group.

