### Outcomes

The primary outcomes for patients are reduced complications and less sedative medication during CC (documented by nurses at the CC lab), and less tension/strain (physiological parameters like pulse, blood pressure, heart frequency), perceived stress (PSS) and better mood (POMS) measured by established and validated self-report questionnaires. Further secondary outcomes for patients are better pre- and post-operative wellbeing, chronic stress (TICS), depression and anxiety (HADS), panic disorder, psychosocial functioning (PHQ-9), life events (ILE), general health (SF-12), satisfaction with health and sleep (41). Additionally, patients are asked about their life style, socioeconomic status and satisfaction about the intervention. At the CC lab, nurses document the behavior of the patients during the cardiac catheterization (agitation, duration of hospital stay, tranquilizer/sedativa use, and level of information) and the number of complications occurred during the procedure. The primary outcomes for practitioners—perceived (PSS) and chronic stress (TICS)—are measured by established and validated self-report questionnaires. Additionally, stress load and recovery are assessed by physiological measurements: circadian profile of HRV (42–44), saliva cortisol (45), alpha-amylase (46) and lysozyme on two working/lab days and two days off as well as the following night, prior to and after the intervention, respectively. The HRV measurements base on beat-to-beat R-R intervals and comprises outcomes for the total activity of the autonomic nervous system [standard deviation of RR intervals (SDNN)], parasympathetic function [root mean sum of squared distance (RMSSD)] and stress load and recovery (number and percentage of R-R intervals lower or >50 msec). Saliva samples are taken on nine defined time points during the day (immediately after awakening, 30, 45, 90, 150 min after awakening, before lunch, 4 p.m., before dinner and going to bed) on a working/lab day and day off. Weight and mood (POMS) are assessed simultaneously as control variables. The practitioners are further asked about vital exhaustion (VE), anxiety and depression (HADS), tension, effort-reward imbalances (ERI), social support (BSSS), satisfaction with health and sleep (41) as well as life style, socioeconomic status, expectations and adherence (barriers) to the intervention program.

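### Patient analysis: sedative medication is a primary outcome and also a control or stratification variable, and adherence is used the same way, so the adjusted or stratified contrasts do not estimate the total randomised effect

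*Protocol article*

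**What the plan says.** The Outcomes section opens its patient list with: "The primary outcomes for patients are reduced complications and less sedative medication during CC". The Statistical Analysis section gives the patient model: "The data of the patients will be analyzed according to a multivariate variance analysis (between-subject factor: intervention group vs. control group". The next sentence reads: "Sociodemographic data, sedative medication, adherence to the intervention will be implemented as control variables or stratification variables for subgroup analysis".

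Two statements under Experimental Procedure/Intervention fix the timing. On the intervention: "The video is shown to the patients the day before the CC via a tablet bedside in the clinic". On sedation: "patients get sedatives if needed and the type of sedative and dose is documented". The same section says that sedation is not routine and that only the intervention group receives the intervention. The randomisation list was drawn up before recruitment (Randomization Procedure and Blinding).

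The article does not confine sedation or adherence to a secondary, sensitivity or mediation analysis, and it does not name an unadjusted comparison as primary.

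**The concern.** A covariate or subgroup factor in a randomised comparison should not be something that treatment can change. The video teaches ways to handle anxiety and tension. Sedation is given when a patient needs it, and the protocol itself expects the video to reduce it. On the protocol's own reasoning, sedation is a consequence of allocation.

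Once the analysis conditions on sedation, the patients compared are no longer comparable by randomisation. A sedated video patient and a sedated control reached sedation under different conditions. Part of the effect may be adjusted away, and unmeasured anxiety that drives both sedation and outcome can enter the contrast.

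Adherence raises a related problem. Only the video arm can adhere, so in a between-arm model it is either undefined for controls or nearly collinear with arm.

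The other patient outcomes put through this analysis are at stake, such as mood, pulse and blood pressure, as is the sedation outcome itself.

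**Working it through.** The plan gives no figure on this point. Its stated power of 0.93 (Sample Size Determination) plays no part here. The check has a logical part and an illustrative part.

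**1. Order of events.** Allocation list, then M1 questionnaire, then video (day before), then catheterization with sedation as needed, then M2 questionnaire. Sedation follows both randomisation and the video, so it is not a baseline covariate. The medication item in Table 1 is a lifestyle factor recorded at M1 and M3. It is not sedation during the procedure.

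**2. Sedation as outcome and covariate in one model.** The covariate explains the outcome completely, so the adjusted arm effect is zero by construction.

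**3. Sedation as covariate for another outcome.** In a linear model, adjusted effect = total effect − b × (p_video − p_control). Here p is the proportion sedated and b the coefficient of sedation in the adjusted model. If higher scores are worse and the video lowers both score and sedation, a positive b shrinks the effect and a negative b inflates it.

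**4. Illustration.** All inputs are assumptions:
- Tension D has SD 1, and the video lowers it by 0.5.
- Liability to sedation is L = r·D + √(1 − r²)·noise.
- A patient is sedated when L exceeds the cut that gives a control rate of 10%, 20% or 30%.
- The outcome is Y = 0.7·D + k·(sedated) + noise, where k is the direct effect of sedation.

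With k = 0 the total effect is 0.7 × (−0.5) = −0.35 SD. At r = 1:
- 10% control rate: sedation 10.0% vs 3.8%, b = 1.43; adjusted = −0.35 + 1.43 × 0.062 = −0.26.
- 20%: 20.0% vs 9.0%, b = 1.28; adjusted = −0.35 + 1.28 × 0.110 = −0.21.
- 30%: 30.0% vs 15.3%, b = 1.20; adjusted = −0.35 + 1.20 × 0.147 = −0.17.

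Shrinkage with k = 0, from large simulated samples:

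| r (tension with sedation liability) | 10% | 20% | 30% |
|---|---|---|---|
| 1.0 | 25% | 40% | 51% |
| 0.7 | 14% | 21% | 26% |
| 0.5 | 7 to 8% | 11% | 14% |
| 0.3 | 3% | 4% | 5% |

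**5. Direct effect of sedation.**
- r = 1, k = +0.3, 30% rate: total = −0.35 + 0.3 × (0.153 − 0.300) = −0.394. The adjusted effect stays at −0.172, so shrinkage is 1 − 0.172/0.394 = 56% (57% if −0.17 is used).
- r = 1, k = −0.3, 10% rate: shrinkage is about 21%.
- r = 0.5, k = −1.0, 30% rate (30.0% vs 21.9%): total = −0.35 + 1.0 × 0.081 = −0.269, adjusted = −0.301. The effect is inflated by 0.301/0.269 − 1 = 12%. At 10% and 20% the inflation is about 4% and 8%.

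**6. Stratifying.** At r = 1, k = 0 and a 20% rate, the within-stratum effects are about −0.23 (not sedated) and −0.07 (sedated), against a total of −0.35.

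**7. No true effect on the outcome.** Suppose an anxiety trait drives both sedation and outcome, and the video lowers only sedation (simulated 31% vs 16%, b = 0.43). The adjusted difference is then 0 − 0.43 × (0.162 − 0.312) = +0.06 SD, although the true difference is zero.

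**8. Sensitivity to other assumptions.** Use the identity in step 3 with a total of 0.50 SD and sedation halved by the video from 20%, 30% or 40%. A coefficient b of 0.5 to 1.0 in size moves the estimate by 0.05 to 0.20 SD, which is 10% to 40%. It goes down if sedated patients score worse and up if sedatives lower the score. The 12% above is therefore a result for its setting, not a bound.

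**The case against.** The strongest defence is that the sentence is ambiguous. The preceding sentence names arm as the only between-subject factor, and the reference to subgroup analysis could qualify both uses, which would leave the main comparison unadjusted. That is a possible reading. It does not clear the plan, because the text does not say so and subgroups formed by sedation break the randomised comparison as well.

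The objection on size stands. Shrinkage of 25% to 51% needs tension to determine sedation completely. Looser links give 3% to 26%, and since the protocol describes sedation as non-routine, nothing in it supports the higher rates. Perceived stress, the criterion used for sample size, is measured in patients only at M1 and M3 (Table 1). A 0.7 loading on procedural tension is therefore more plausible for M2 mood or procedural measures than for that outcome.

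The adherence point is smaller for patients. The video lasts 10 minutes and is shown at the bedside, and the adherence discussion mostly concerns the practitioners' programme.

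Three stronger readings may tempt a reader, and the documents do not support them:
- **Adjustment must hide a real benefit.** Steps 5, 7 and 8 show that it can also inflate an effect or create a difference.
- **Adherence is a primary outcome.** It is not listed as one. It is only a post-randomisation variable.
- **The practitioner part has the same error.** The Outcomes section says of practitioners: "Weight and mood (POMS) are assessed simultaneously as control variables". However, Statistical Analysis describes mainly descriptive work and within-person physiological comparisons, and states no arm effect adjusted for mood after the programme.

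**Conclusion.** The point holds for the patient analysis. The Outcomes and Statistical Analysis sections give sedation incompatible roles, and nothing in the article reconciles them. Adherence is wrongly placed in the same list because it arises after randomisation and exists in one arm only. Whether used as covariates or as strata, these variables yield contrasts that no longer estimate the total randomised effect.

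This conclusion rests on the stated timing and needs no assumed number. Its size cannot be fixed from the documents. In the simulations with assumed control sedation rates of 10% to 30%, it runs from about 3% to 51% shrinkage with no direct sedative effect, to about 56% with a direct effect of +0.3 SD, and to about 12% inflation with a direct effect of −1.0 SD. Direction and size both depend on why patients are sedated and what sedation does to the outcome.

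**What to change.** In Statistical Analysis, for the between-arm effectiveness analysis in patients:
- Remove sedative medication and adherence from the control and stratification variables.
- Analyse sedation as an outcome, compared by arm.
- Restrict covariates to variables measured before randomisation, or at M1 before the video is shown, for example sociodemographic data and the M1 value of the outcome.
- Describe adherence within the intervention arm.
- Label any analysis that conditions on sedation as secondary (mediation or sensitivity). Such an analysis is legitimate and need not be forbidden.

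The cost is a rewrite of one sentence, with a short addition. Sample size, data collection and significance level do not change.
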